# Open-label, randomized multicentre phase II study to assess the efficacy and tolerability of sunitinib by dose administration regimen (dose modification or dose interruptions) in patients with advanced or metastatic renal cell carcinoma: study protocol of the SURF trial

**DOI:** 10.1186/s13063-018-2613-8

**Published:** 2018-04-12

**Keywords:** Renal cell carcinoma, Sunitinib, Metastatic, Schedule, Toxicity, Safety, Health-related quality of life

## Abstract

**Background:**

Sunitinib is a tyrosine kinase inhibitor approved in the first-line metastatic renal cell carcinoma (MRCC) setting at the dose of 50 mg daily for 4 weeks followed by a pause of 2 weeks. Due to toxicity, this standard schedule (50 mg daily 4/2) can induce up to 50% of sunitinib dose modification (reduction and/or interruption). The current recommendation in such case is to reduce the dose to 37.5 mg per day (standard schedule 4/2). Recent data highlight an alternative schedule: 2 weeks of treatment followed by 1 week of pause (experimental schedule 2/1). The SURF trial is set up to evaluate prospectively experimental schedule 2/1 when toxicity occurs. This article displays the key elements of the study protocol.

**Methods/design:**

SURF [NCT02689167] is a prospective, randomized, open-label phase IIb study. Patients are included at sunitinib initiation while receiving standard schedule 4/2 (50 mg daily) according to the marketing authorization indication. When a dose adjustment of sunitinib is required, patients are randomized between standard schedule 4/2 (37.5 mg daily) and experimental schedule 2/1 (50 mg daily). Key eligibility criteria are the following: patients with locally advanced inoperable or MRCC who are starting first-line treatment with sunitinib, with histologically or cytologically confirmed renal cancer clear cell variant or with a clear cell component, and with Karnofsky performance status ≥70%. The primary objective is to assess the median duration of sunitinib treatment (DOT) in each group. The key secondary objectives are progression-free survival, overall survival, time to randomization, objective response rate, safety, sunitinib dose intensity, health-related quality of life, and the description of main drivers triggering randomization. We hypothesized that experimental schedule 2/1 would result in an improvement in median DOT from 6 to 8.5 months. It was estimated that 112 patients would be needed in each arm during 24 months. In order to take into account the possibility of treatment discontinuation before randomization, 248 patients are necessary.

**Discussion:**

The SURF trial is asking a pragmatic question adapted to the current practice on what is the best way to adapt sunitinib when treatment-related adverse events occur. The results of the SURF trial will bring high-value data to support the use of an alternative schedule in sunitinib treatment.

**Trial registration:**

ClinicalTrials.gov, NCT02689167. Registered on 26 February 2016.

**Electronic supplementary material:**

The online version of this article (10.1186/s13063-018-2613-8) contains supplementary material, which is available to authorized users.

## Background

Metastatic renal cell carcinoma (MRCC) represents nearly 85% of all kidney cancers. More than 120,000 cases of RCC are being diagnosed each year in Europe and in the USA, and the incidence of RCC seems to be rising.

Sunitinib is an anti-angiogenic tyrosine kinase inhibitor (TKI) indicated for the treatment of advanced or MRCC in adults. It is mainly used in the first-line setting at the initial dose of 50 mg taken orally once daily for 4 consecutive weeks followed by a 2-week rest period to comprise a complete cycle of 6 weeks (schedule 4/2). Recommendations in case of required dose modification indicate a dose reduction to 37.5 mg per day and if necessary further to reduce the dose to 25 mg daily [1]. Another promising adjustment schedule is to continue with the daily dose of 50 mg while making more frequent break periods: 2 weeks of treatment followed by a pause of 1 week (schedule 2/1). This last regimen is expected to reduce adverse events and preserve health-related quality of life (HRQoL) while maintaining the same dose intensity. Maintaining exposure to sunitinib seems essential based on previously reported data linking exposure to drug activity in the MRCC setting [2–4]. The experience of the Cleveland Clinic with 30 patients treated with schedule 2/1 showed a significant improvement in the tolerance for the drug, without grade 4 toxicity and with less than 30% of patients with grade 3 toxicity [5].

In a multicentre one-arm prospective study, 60 patients were treated with 50 mg on schedule 2/1, but it did not result in a lower rate of grade III or higher fatigue and diarrhea when compared to historical data from trials employing schedule 4/2. However, efficacy data showed a robust response rate and a prolonged progression-free survival, suggestive of improved long-term tolerability in patients receiving sunitinib on schedule 2/1 [6]. In another prospective phase II study of an individualized sunitinib schedule, 22 patients got sunitinib 50 mg schedule 2/1 as the optimal schedule with good efficacy on the overall response rate (ORR), progression-free survival (PFS), and overall survival (OS) [7]. Sunitinib administered with schedule 2/1 was associated with less toxicity and higher failure-free survival (FFS) at 6 months than that administered with schedule 4/2, without compromising the efficacy in terms of ORR and time to progression (TTP) in a multicentre, randomized, open-label phase II trial, where 38 patients were treated with schedule 2/1 [8]. Many retrospective studies showed better tolerance and efficacy of schedule 2/1 such as the RAINBOW cohort [9, 10]. The main drawback of these data comes from their retrospective status and the small size of the populations for the prospective trials.

The SURF trial aims at evaluating prospectively at a larger scale the efficacy and safety of sunitinib according to the adaptation of the administration regimen (schedule 4/2 or 2/1) in patients with advanced or MRCC. This article displays the key elements of the study protocol.

## Methods/design

### Study design

SURF is a prospective, multicentre, randomized, open-label study in which patients are randomized between two medication schedules (standard schedule 4/2 vs experimental schedule 2/1) when a dosage adjustment (e.g., adverse event, patient request) of sunitinib is required (Additional file 1). Standard schedule 4/2 is defined as 2 periods comprising 4 weeks “on” with sunitinib followed by 2 weeks “off” without sunitinib. The experimental schedule 2/1 is defined as 2 periods comprising 2 weeks “on” with sunitinib followed by 1 week “off” without sunitinib.

At the inclusion, all patients start sunitinib at the recommended schedule 4/2 with sunitinib dosage of 50 mg once daily. When a dosage adjustment of sunitinib is required, patients will be randomized between two arms: one arm in which the dose of sunitinib is reduced to 37.5 mg once daily (standard schedule 4/2, arm 4/2) and one arm in which treatment is administered with a dose maintained at 50 mg once daily (experimental schedule 2/1, arm 2/1) (Fig. 1).

**Fig. 1 Fig1:**
[figure not shown]
Trial design

The aim of this randomized clinical trial is to establish whether experimental schedule 2/1 is acceptable in terms of efficacy and toxicity. The main hypothesis is that experimental schedule 2/1 may maintain efficacy in terms of duration of treatment, survival rate, and response rate, has less toxicity, and preserves HRQoL.

### Endpoint definitions

#### Primary endpoint

The primary objective of this study is to estimate the median duration of treatment (DOT) in each treatment group (arm 4/2 vs arm 2/1) calculated from sunitinib initiation (Fig. 2).

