### Study procedures and randomization

Patients candidate for first-line treatment with sunitinib and meeting the inclusion/exclusion criteria will be offered participation in the protocol. All the included patients will receive sunitinib 50 mg once daily with schedule 4/2 according to the marketing authorization indication.

When the investigator believes a modification of administration of sunitinib is necessary, the patient will become eligible for randomization. Randomization will take place in all study sites using an IWRS type of centralized system.

Randomization will be performed according to a ratio of 1:1 using minimization technique with stratification according to:centreTime to randomization: time between initiation of sunitinib and dose adjustment (<6 or ≥6 months)Heng prognostic factors at baseline (good and intermediate prognosis groups vs poor prognosis group)

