### Statistics and data analysis

#### Sample size

The main objective of this randomized phase II trial is to evaluate the median DOT in each arm.

TThe following hypotheses will be tested: H0 (null hypothesis of inefficiency): median DOT of 6 months [15, 16] and H1 (alternative efficiency hypothesis): median DOT of 8.5 months. A Brookmeyer-Crowley type of test will be used to estimate the median. With a one-sided statistical test of significance (*α* 5%) and a power of 80%, it will be required to include 112 patients in each arm for 24 months with at least 12 months of follow-up.

The approximate upper critical value to reject H0 is 7.66 months. The number of patients is increased by 10% to take account of the potential progression or treatment discontinuation by patients before randomization and patients lost to follow-up. It will therefore be necessary to include 248 patients.

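### Primary duration of treatment includes event-free time before randomisation and is tested against a fixed 6-month median, so the stated one-sided 5% error is not assured

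*Protocol article*

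**What the plan says.** All places are in the protocol article.

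- **Clock and population (Primary endpoint).** Median DOT is estimated "in each treatment group (arm 4/2 vs arm 2/1) calculated from sunitinib initiation".
- **Entry to an arm (Study design).** "When a dosage adjustment of sunitinib is required, patients will be randomized between two arms". All patients start on the same schedule, and there are no arms before that moment.
- **Test (Sample size).** "H0 (null hypothesis of inefficiency): median DOT of 6 months", set against "H1 (alternative efficiency hypothesis): median DOT of 8.5 months". The method is named as follows: "A Brookmeyer-Crowley type of test will be used to estimate the median". It is one-sided at 5% with 80% power, 112 patients per arm, and an upper critical value of 7.66 months. The number is raised by 10% to 248 for progression or discontinuation before randomisation and for loss to follow-up.
- **Stratification (Study procedures and randomization).** One factor is "time between initiation of sunitinib and dose adjustment (<6 or ≥6 months").
- **Secondary endpoints.** Time from randomisation to discontinuation, by arm, and time to randomisation are both listed.
- **Analyses of time-to-event data.** Kaplan-Meier medians are given per arm. The treatment effect is a hazard ratio with its confidence interval, without a P value.

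**The concern.** A patient who stops sunitinib before needing an adjustment never belongs to an arm. Everyone who does belong to one has therefore survived, on drug, the whole interval from initiation to randomisation. Counting that interval in DOT adds guaranteed time to each arm's median, and the total is then compared with a fixed external value. The 10% inflation replaces patients lost before randomisation but does nothing about the guaranteed time carried by those who remain.

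The stratification shows the problem plainly: a patient randomised at 6 months or later has already reached the null value before taking any randomised treatment.

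At stake is the error rate of the only test on which the hypotheses, the critical value and the sample size rest. An arm could clear 7.66 months because its patients were randomised late.

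**Working it through.** **Inputs.** From Sample size: null median 6 months, alternative 8.5, one-sided 5%, 112 per arm, cut-off 7.66, at least 12 months of follow-up (so no administrative censoring before 6 months). From Sample size and Discussion: 10% loss before randomisation. Assumed, because not stated: exponential DOT, the benchmark describing all starters from initiation, and adjustment time independent of DOT.

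**1. The plan's own figure.** Under the alternative, S(6) = 0.5^(6/8.5) = 0.613. For a one-sample test of S(6) = 0.5,

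N = (1.645 + 0.842)² × 0.613 × 0.387 / (0.613 − 0.5)² ≈ 115,

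with power 79.2% at 112. This matches 112 closely, so the design is a one-sample test in each arm. The cut-off reproduces only roughly (7.35 to 7.58 months, depending on the variance form, against 7.66). Also 112 × 1.1 = 123.2, rounded up to 124 per arm, or 248. Without selection, simulated rejection under the null is 3% to 5%.

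**2. Adding the selection.** Let DOT be exponential with median 6 months in all starters and the time at which an adjustment is needed be exponential, and let neither schedule have an effect. Let q be the share reaching randomisation. Among randomised patients, DOT from initiation has

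S(t) = [0.5^(t/6) − (1 − q) × 0.5^(t/(6(1 − q)))] / q.

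At q = 0.9: S(6) = (0.5 − 0.1 × 0.00098)/0.9 = 0.555 and S(7.66) = (0.4128 − 0.1 × 0.00014)/0.9 = 0.459.

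The test at 6 months rejects when the share still on drug exceeds 0.5 + 1.645 × 0.5/√112 = 0.578, that is, at least 65 of 112. The other rule rejects when the arm's median exceeds 7.66. Binomial tails with n = 112 (simulation agrees to about one percentage point):

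| Lost before randomisation | S(6) | S(7.66) | Median DOT (months) | Median above 7.66 | Test at 6 months rejects |
|---|---|---|---|---|---|
| 10% | 0.555 | 0.459 | 6.9 | 19% | 33–34% |
| 20% | 0.617 | 0.513 | 7.9 | 61% | 82% |
| 30% | 0.672 | 0.567 | 8.8 | 92% | 98% |

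At 30% loss the null median already exceeds the alternative of 8.5 months.

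**3. Fixed time to randomisation G instead.** The median among randomised patients is G + 6, which passes 7.66 once G exceeds 1.66 months. Rejection per arm is 18% to 34% at G = 0.91 (10% lost, since 0.5^(0.91/6) = 0.90), 37% to 61% at G = 1.38 (one 6-week cycle), and 96% to 100% at G = 3.

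**4. If patients needing adjustment have a shorter underlying DOT.** Replace 6 by u in the formula.

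| u (months) | Loss | Median DOT (months) | Rejection, both rules |
|---|---|---|---|
| 5 | 10% | 5.8 | 1% to 3% |
| 5 | 30% | 7.4 | 35% to 66% |
| 4 | 10% | 4.6 | about 0% |
| 4 | 30% | 5.9 | under 1% to 4% |

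**5. After the change.** In simulation with u = 6, the randomisation clock returns the null median to 6.0 months and rejection to 5.2% to 5.6%. Delayed entry gives 5.7% to 6.3%. A one-sided between-arm test has size 5.1% even with the initiation clock.

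**6. Power between arms.** Taking the hazard ratio as 6/8.5, Schoenfeld's formula gives 4 × (1.645 + 0.842)²/[ln(8.5/6)]² = 204 events; Freedman's gives 208. The final analysis is set at 112 events (Study duration). If that is the total over both arms, power is Φ(0.348 × √112/2 − 1.645) = Φ(0.20), about 58%.

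**The case against.** The strongest reply concerns the benchmark. The article cites two sources for the 6 months without describing their population or clock. The abstract speaks of schedule 2/1 improving median DOT from 6 to 8.5 months. That can be read as 6 months being expected from initiation in dose-adjusted patients on the comparator. On that reading the null already contains the pre-randomisation time and the inflation disappears. This stands as a possibility, but the article does not say it.

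Second, adjustment is triggered by adverse events or patient request, so independence from DOT is doubtful. This also stands: step 4 shows that the bias can vanish or reverse when such patients have a shorter DOT and are randomised early.

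Third, the analysis plan and the outcome-definition figure are not shown, so silence on delayed entry proves nothing. Accepted; the point rests on the stated clock and the stated null, not on that silence.

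A reader might infer three stronger things that the article does not support:

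- **That both arms will reject with no treatment effect.** At 10% loss with a fixed time to randomisation, both reject in only about 8% of simulated trials. Near-certainty needs randomisation at roughly 2 to 3 months or later, and no such times are given. The abstract also ties the hypothesis to schedule 2/1 alone.
- **That the 6-month null is false by construction.** That holds only for patients randomised at 6 months or later, a group whose size is not stated.
- **That the comparison of schedules is biased.** The guaranteed time is shared by both arms, and time to randomisation is a minimisation factor.

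**Conclusion.** The point holds as a defect in the one-sample primary test. Event-free time is counted towards a fixed threshold, so the nominal 5% is not assured. If the benchmark describes unselected starters and need for adjustment is independent of DOT, the per-arm error is about 19% to 34% at the plan's own 10% loss and above 90% at 30%. If the underlying median is 4 to 5 months in those needing adjustment and they are randomised early, the error can be at or below 5%. The article does not supply the quantities that would settle which case applies, so the actual error is unknown rather than known to be high. The between-arm hazard ratio under the null is unaffected.

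**What to change.** 1. Make time from randomisation to sunitinib discontinuation the primary DOT. If the initiation clock is kept, estimate it with delayed entry at the randomisation date. Delayed entry relies on randomisation time being independent of DOT, so moving the clock is the safer choice.
2. Base the conclusion about schedule 2/1 on the between-arm hazard ratio with its confidence interval.
3. Do not interpret the one-sample test against 6 months unless the null is restated, with its source population, for the clock and population actually used. Restate the 7.66-month cut-off and the power to match.
4. Report the distribution of time to randomisation by arm beside the primary result.

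**Cost.** The endpoint change needs only wording, since both dates are available from the treatment records and the randomisation system. Reported medians will be shorter and less easily set beside published figures counted from initiation. A restated null needs a benchmark that the article does not contain. The 80% power does not carry over to comparing arms: 204 to 208 events would be needed against 112 planned. The plan should state the precision achievable for the hazard ratio instead.

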**Fig. 2 Fig2:**
[figure not shown]
Outcome definition

#### Secondary endpoints

The key secondary objectives are measured to evaluate the efficacy and the safety of the experimental schedule 2/1 and are the following: are measured to evaluate the efficacy and the safety of experimental schedule 2/1:To estimate the PFS and OS of patients in each of the groups and in the overall population included in the studyTo describe the decision factors requiring dose adjustment leading to randomization to the dose of sunitinibTo estimate the time between the date of randomization and the treatment discontinuation (regardless of the cause) in the two treatment armsTo estimate the time to randomization defined as the delay between the date of initiation of treatment and the date of randomizationTo evaluate ORR, duration of response, and clinical benefit duration according to RECIST 1.1 criteria [11]To describe the toxicity before and after randomization according to NCI CTCAE version 4.0To describe dose modifications (dose reduction, interruption, or discontinuation) and to estimate the dose intensity in each treatment groupTo evaluate HRQoL from the initiation of treatment (before, during, and after randomization)To estimate time to HRQoL deterioration (TTD) in each of the groups and in the overall population included in the study

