### Analyses of time-to-event data

The median duration of treatment and other survival rates will be estimated using the Kaplan-Meier method. Median survival will be described with their confidence intervals (one-sided statistical test of significance (*α* 5%)) in each of the arms.

Survival curves will be calculated by the Kaplan-Meier method and described using their medians and their 95% confidence intervals.

Multivariate Cox analysis will be conducted to identify factors potentially influencing survival.

All variables originally collected will be tested by univariate analysis. The variables with *P* ≤ 0.20 will be eligible in multivariate analysis.

No *P* value will be indicated, and the effect size of treatment will be assessed using the HR with its confidence interval.

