## Discussion

At the time this manuscript was written, 80 patients have been included in the SURF trial, which makes it the largest prospective cohort of patients assessing the question of alternative schedule 2/1 of sunitinib. In comparison to the current available data, this trial will be able to provide more robust data about an alternative schedule of sunitinib based on an academic study.

The SURF trial is asking a pragmatic question adapted to the current practice: what is the best way to adapt sunitinib when side effects occur? In the SURF trial, randomization does not occur at the start of sunitinib but when a dose modification is required. The decision to randomize the patient is based on the choice of the physician. The purpose of the SURF trial is to bring robust prospective data of efficacy and side effects that can sustain the use of alternative schedule 2/1 in clinical routine practice. Furthermore, HRQoL data evaluated by the EORTC QLQ-C30 questionnaire will bring patient perspective on the alternative schedule.

One of the limitations of this design is a potential loss of power depending on the number of patients who may leave the study before randomization. We estimated that 10% of the patients could be lost between the initiation of the treatment and a potential randomization.

Recently, the FDA [17] approved sunitinib in an adjuvant setting for high-risk patients following the results of the S-TRAC trial, showing that sunitinib improved PFS in high-risk patients [18]. In this trial, patients started sunitinib at 50 mg with schedule 4/2. When toxicity occurred, dose interruptions or dose reductions to 37.5 mg per day were allowed, depending on the type and severity of the toxicity. An alternative schedule was not allowed. In the sunitinib arm, 48.8% of patients had grade III adverse events and 12.1% grade IV adverse events. Furthermore concerning HRQoL, on most QLQ-C30 subscales, patients in the sunitinib group had lower scores than those in the placebo group. Dose reductions and interruptions because of adverse events occurred in 34.3% and 46.4%, respectively, of the patients in the sunitinib group, and treatment discontinuations owing to adverse events occurred in 86 patients (28.1%) in the sunitinib group. In this setting, improving the management of side effects and maintaining HRQoL will be a high-priority topic.

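### Time to randomization can be computed only for patients who reach randomization, and the only time-to-event method stated, Kaplan-Meier, would censor patients who stop for good beforehand; a cumulative incidence in all included patients would serve better

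*Protocol article*

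**What the plan says.** The Secondary endpoints section of the protocol article sets out to "estimate the time to randomization defined as the delay between the date of initiation of treatment and the date of" randomization. The abstract gives the endpoint key status: "The key secondary objectives are progression-free survival, overall survival, time to randomization, objective response rate".

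The first date exists for everyone: "At the inclusion, all patients start sunitinib at the recommended schedule 4/2 with sunitinib dosage of 50 mg once daily" (Study design). The second date depends on a later judgement: "When the investigator believes a modification of administration of sunitinib is necessary, the patient will become eligible for randomization" (Study procedures and randomization).

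The plan expects that some patients will not get that far: "We estimated that 10% of the patients could be lost between the initiation of the treatment and a potential randomization" (Discussion). The Sample size section adds 10% for the same reason and for loss to follow-up. On how common dose changes are, the abstract says that the standard schedule "can induce up to 50% of sunitinib dose modification".

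The section on time-to-event data gives one method: "The median duration of treatment and other survival rates will be estimated using the Kaplan-Meier method". It does not name time to randomization. In the list of secondary objectives, the items on PFS and OS and on time to HRQoL deterioration name the overall included population; time to randomization names no population.

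**The concern.** A patient who permanently stops sunitinib or dies before any adjustment has a start date and no randomization date. The text leaves two routes for such a patient.

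- **Take the definition literally.** The delay is computed where both dates exist. The result is conditional on having been randomized and, for the cohort that started treatment, looks too early.
- **Apply Kaplan-Meier to all included patients.** Those who stopped are censored. Kaplan-Meier then treats them as still able to be randomized later, which they are not. One minus Kaplan-Meier overstates the share ever randomized.

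The trial asks how to adapt sunitinib once an adjustment is needed, and this endpoint reports when patients reach that point. The cohort is followed from initiation, so it can give an undistorted answer. At stake is the accuracy of one descriptive result, not the primary endpoint or any contrast between arms.

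**Working it through.** **The plan's own figures.** The article gives no expected value for time to randomization, so there is none to reproduce. The related planning figure does reproduce: 112 × 1.1 = 123.2, rounded up to 124 per arm, and 2 × 124 = 248. The allowance is 248 − 224 = 24 patients, or 24/248 = 9.7%, which agrees with the 10% in the Discussion.

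**Model (assumed).** Two competing constant hazards from treatment start: randomization (r) and permanent stopping or death without randomization (s). Let p be the share ever randomized, p = r/(r + s).

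- Median among the randomized only: ln 2/(r + s)
- Kaplan-Meier median, stoppers censored: ln 2/r
- Cumulative incidence of randomization: p × [1 − exp(−(r + s)t)]
- Time to 50% cumulative incidence: −ln(1 − 0.5/p)/(r + s), which exists only if p > 0.5
- One minus Kaplan-Meier: 1 − exp(−rt)

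The Kaplan-Meier median divided by the randomized-only median is (r + s)/r = 1/p, whatever the stopping hazard: 1.11 at p = 0.9 and 2 at p = 0.5. In the long run, one minus Kaplan-Meier tends to 100% while the cumulative incidence tends to p, so the gap tends to 1 − p.

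**Values of p.** 0.9 corresponds to the planned 10% loss. 0.5 takes the abstract's upper figure for dose modification as the share randomized. 0.7 lies between them.

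**Set A: stopping has a 6-month median.** This value is borrowed from the H0 median duration of treatment in the Sample size section: s = ln 2/6 = 0.1155 per month, r = s × p/(1 − p).

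| p | r + s | Randomized-only median (months) | Kaplan-Meier median | Time to 50% cumulative incidence | One minus Kaplan-Meier at 12 months | Cumulative incidence at 12 months |
|---|---|---|---|---|---|---|
| 0.9 | 1.155 | 0.60 | 0.67 | 0.70 | 100% | 90% |
| 0.7 | 0.385 | 1.8 | 2.6 | 3.3 | 96% | 69% |
| 0.5 | 0.231 | 3.0 | 6.0 | not reached | 75% | 47% |

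For p = 0.5 in full: r = s = 0.1155; ln 2/0.231 = 3.0; ln 2/0.1155 = 6.0; 0.5 × (1 − exp(−0.231 × 12)) = 0.5 × 0.9375 = 46.9%; 1 − exp(−0.1155 × 12) = 75%. At 6 months the cumulative incidence is 0.5 × 0.75 = 37.5%.

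**Set B: median among the randomized fixed at 3 months (also assumed).** Here r + s = ln 2/3 = 0.231 and r = p × 0.231.

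| p | Randomized-only median (months) | Kaplan-Meier median | Time to 50% cumulative incidence | One minus Kaplan-Meier at 12 months | Cumulative incidence at 12 months |
|---|---|---|---|---|---|
| 0.9 | 3.0 | 3.3 | 3.5 | 92% | 84% |
| 0.7 | 3.0 | 4.3 | 5.4 | 86% | 66% |
| 0.5 | 3.0 | 6.0 | not reached | 75% | 47% |

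**Cross-check against the design.** Randomization is stratified at 6 months from initiation, so the plan allows for late randomizations. In Set A the share of randomizations after 6 months is exp(−6 × 1.155) = 0.1% at p = 0.9 and exp(−6 × 0.231) = 25% at p = 0.5. The Set A row for p = 0.9 therefore fits the stratification badly. Set B gives 25% in every row and shows the same ordering of the three medians.

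**The case against.** The text commits to neither route. The definition gives a start and an end, as any time-to-event endpoint does; it does not confine the analysis to randomized patients. The Kaplan-Meier sentence does not name this endpoint. The article condenses a full protocol that is not shown, the figure on outcome definition is missing from the text at hand, and a statistical analysis plan may well set the population, censoring and competing-event rules. The delay among randomized patients is also a legitimate description in its own right.

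All of this stands, and it rules out several stronger readings.

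- A reader might infer that the endpoint is wrong as it stands. The documents support only that it would mislead about the included cohort under either route that they leave open.
- A reader might infer that both dates are confined to randomized patients. Only the randomization date is.
- A reader might take the endpoint as the trial's measure of how often sunitinib needs adjusting. The article asks for a delay, and the crude share randomized follows from the enrolment counts.

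The figures have limits too. The 6-month value is the H0 median for total duration of treatment in an arm, not a rate of stopping without adjustment. The 50% is an upper figure for toxicity-driven modification, whereas randomization can also follow a patient's request.

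What remains is that the article gives both a definition and a general method, and neither gives an undistorted figure for all who started treatment.

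**Conclusion.** The point holds as a minor one. For patients who stop for good or die before randomization, the definition and the only stated time-to-event method lead to dropping them or to censoring them. The first makes the delay look too short for the included cohort; the second makes one minus Kaplan-Meier overstate the share randomized.

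At the planned 10% loss the medians hardly move: 0.60, 0.67 and 0.70 months in Set A, or 3.0, 3.3 and 3.5 in Set B. The 12-month share is overstated by 8 to 10 percentage points. At 50% never randomized the effect is large: 3.0 months, 6.0 months and not reached, and 75% against 47% at 12 months. These sizes rest on constant hazards and on assumed values of the stopping rate and of p. The 1/p ratio between the first two medians needs only hazards that are constant.

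The endpoint is descriptive and precedes the treatment comparison. Nothing here alters the duration-of-treatment result or any difference between arms.

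**What to change.** Define time to randomization in all included patients, from sunitinib initiation, as a cumulative incidence (Aalen-Johansen estimator). Treat permanent discontinuation or death before randomization as the competing event, and censor patients who are still on treatment and not yet randomized at the data cut-off. Report the share randomized, with confidence intervals, at fixed times such as 3, 6 and 12 months. Keep the delay among randomized patients, labelled as a description conditional on randomization. If the full protocol or the statistical analysis plan already says this, no change is needed there.

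The cost is analysis wording only: initiation, randomization, discontinuation and death dates are collected or recorded in any case. The one drawback is that a median may not exist if half or fewer of the patients are randomized; the shares at fixed times then take its place.
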